## Abstract

**Background:**

In the nursing home population, it is estimated that 1 in every 3 patients is polymedicated and given their considerable frailty, these patients are especially prone to adverse drug reactions. Clinical pharmacist-led medication reviews are considered successful interventions to improve medication safety in the inpatient setting. Due to the limited available evidence concerning the benefits of medication reviews performed in the nursing home setting, we propose a study aiming to demonstrate a positive effect that a clinical decision support system, as a health care intervention, may have on the target population. The primary objective of this study is to reduce the number of patients with at least one event when using the clinical decision support system compared to the regular care. These events consist of hospital referrals, delirium, falls, and/or deaths.

**Method/Design:**

This study is a multicentre, prospective, randomised study with a cluster group design. The randomisation will be per main nursing home physician and stratified per ward (somatic and psychogeriatric). In the intervention group the clinical decision support system will be used to screen medication list, laboratory values and medical history in order to obtain potential clinical relevant remarks. The remarks will be sent to the main physician and feedback will be provided whether the advice was followed or not. In the control group regular care will be applied.

**Discussion:**

We strongly believe that by using a clinical decision support system, medication reviews are performed in a standardised way which leads to comparable results between patients. In addition, using a clinical decision support system eliminates the time factor to perform medication reviews as the major problems related to medication, laboratory values, indications and/or established patient characteristics will be directly available. In this way, and in order to make the medication review process complete, consultation within healthcare professionals and/or the patient itself will be time effective and the medication surveillance could be performed around the clock.

**Trial registration:**

The Netherlands National Trial Register NTR5165. Registered 2nd April 2015.

## Background

Polypharmacy is defined as the use of more than a certain number of drugs irrespective of their appropriateness [1, 2]. In the Netherlands, it has been defined as the chronic use of 5 or more drugs from different therapeutic groups or subgroups [3]. In the nursing home population, it is estimated that 1 in every 3 patients is polymedicated [4] and given their considerable frailty, these patients are extra prone to adverse drug reactions. In addition, their management is often challenging given the comorbidities and/or complex organ function impairment [1, 2, 5–8]. Furthermore, polymedicated patients are also at risk of suffering from inappropriate prescribing in the form of underprescription. It has been demonstrated that underprescription increases significantly with the number of medicines used [9]. This situation strengthens the need for routine medication reviews and treatment optimisation [10, 11].

Clinical pharmacist-led medication reviews are considered successful interventions to improve medication safety in the inpatient setting. However, there is limited available evidence of the effects concerning comparable interventions performed in the outpatient setting [1, 12, 13]. In addition, few studies have evaluated health related outcomes resulting from clinical pharmacist interventions in nursing homes. Nevertheless, it has been suggested that most of these studies had major limitations: no control group, no clinical outcome measures, inadequate use of nursing staff to influence change, and data analysis by drug use per provider rather than drug use per patient [6, 8, 10, 11, 13, 14]. Some of these studies were randomised controlled trials performed in the nursing home setting by means of a clinical pharmacists-led medication review; some of them measured the effect of multidisciplinary case conference [6, 15]. In other studies, pharmacists performed the medication reviews and sent suggestions to physicians [8, 10, 16]. Nevertheless, some improvements in patient outcomes have been described [8, 10]. The results from these studies are difficult to compare due to the large differences with respect to the interventions applied, the outcomes studied, the settings, and duration of follow-up after the medication review.

Pharmacotherapy optimisation in nursing home patients relies on the development and assessment of novel healthcare interventions [11]. It is suggested that performing a standardised intervention could potentially lead to a successful medication review; this intervention necessitates pharmacists and physicians collaboration, it should include the complete medical and drug history, and fully availability of laboratory values should be guaranteed [10, 12, 13, 17–20].

In the Netherlands, the Dutch Healthcare Inspectorate (IGZ: Inspectie voor de Gezondheidszorg) expects that a medication review is performed by a physician and a pharmacist in all residents of nursing homes yearly; however, this advice implies substantial extra workload for the involved health care professionals. In addition, in this medication review the information given by the nursing staff and the patient him/herself should also be taken into account.

From our experience, medication reviews involve a time consuming process that takes an average of 90 min per patient. When considering a nursing home of about 150 patients, 450 h a year would have to be dedicated at performing medications reviews.

In daily practice, this unfortunate situation leads to a non-continuous medication review process implying major consequences that may range from an increased number of potential adverse drug reactions, unnecessary hospitalisations and, at worst, death.

Computerised clinical decision support systems (CCDSS) can be defined as decision-aiding tools which provide health care professionals with clinical knowledge and patient-related information, intelligently filtered or presented at appropriate times, so as to enhance patient care [21–23]. Within the SCREEN project (Supporting Clinical Rules in the Evaluation of Elderly patients with Neuropsychiatric disorders), a CCDSS named Clinical Rule Reporter (CRR) has been developed. This system currently analyzes, independently of the applied prescribing software, the medication used by patients in relation to their co-medication, the laboratory data (including renal function), and other relevant clinical data like diagnosis and comorbidities [24]. The CRR combines the clinical rules (algorithms) with the medication list, patient characteristics and laboratory values of the patients in order to obtain concrete advices. These clinical rules or algorithms work with triggers that identify drug related problems like renal or liver dysfunction as well as the need of new medication (stomach protection or laxative agents), the necessity to stop a certain drug or decrease the dose according to age, etc.

Due to the lack of evidence concerning the benefits of medication reviews performed in the nursing home setting, we propose a study aiming to demonstrate a positive effect that the CRR, as a health care intervention, may have on the target population. This population consists of older people (≥65 years) with a high risk of suffering harm when using inappropriate drugs. By this we mean people living in nursing home facilities; these people often suffer from polymedication among other risk factors such as multimorbidity, impaired cognition, renal dysfunction, and increased risk of falling.

The primary objective of this study is to reduce the number of patients with at least one event when using the CRR compared to the regular care. These events consist of hospital referrals, delirium, falls, and/or deaths. Secondary objectives will also be evaluated, including: the analysis within a centre to account for possible differences concerning regular care, the separate analysis for psychogeriatric and somatic wards, the analysis for medication related events (hospital referrals, delirium, falls, and/or deaths), the separate analysis for each of the parameters included in the combined endpoint, the analysis of the quality of life EQ-5D, the analysis of the MAI (Medication Appropriate Index), and finally, a cost analysis.

## Methods/Design

### Study design

The Supporting Clinical Rules Engine in the Adjustment of Medication (SCREAM) study is a multicentre, prospective, randomised study with a cluster group design. The randomisation will be per main nursing home physician and stratified per ward (somatic and psychogeriatric). This study will be blinded for physicians and for patients; physicians will be emphatically requested not to discuss with each other about the study to avoid bias. The study follows the CONSORT guidelines.

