### Overall study design

In order to use the CRR, the nursing homes will have to provide the medication list, the patient characteristics and the laboratory values for each patient in a digital format.

Taking into account the extra workload for the investigators, there will be a predefined day for each nursing home to send the files: nursing home A sends the files on Mondays, nursing home B sends the files on Tuesday, and so on.

All nursing homes will send the patient data both for control and intervention groups.

The randomisation will be performed by two of the authors ([name], [name]). The randomisation will be per main nursing home physician and stratified per ward. Physician A will be randomised in the control group and physician B on the intervention group, taking into account that the amount of patients in each group should be approximately the same.

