#### Intervention group

The datasets will be screened through the CRR on a weekly basis. The messages delivered by the CRR will be sent via mail to the specific physicians. Each remark will be sent on a separate mail in a standardised way. In response to the report, the physician will send a feedback message within 36 h indicating, in a standardised way, whether:the advice was not followedthe advice was followedthe advice was changed.

After receiving this feedback, the investigators will process it in the CRR, in order to create the database for the study.

Additionally, regular care will be also applied. That is according to the Dutch Healthcare Inspectorate, a yearly medication review with a physician and a pharmacist, even though there is a substantial variation [25], For the centres included in this study there are no dedicated clinical pharmacist working in the nursing home.

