### Endpoints

#### Primary endpoint

The primary outcome variable in this study is the proportion of patients with at least one of the events, including hospital referrals (i.e. referral to a specialist, emergency department visit and hospital admission), delirium, falls, and/or deaths. All these events will be reported by the nursing home physician via the electronic questionnaire. To this end the study will assess the differences between regular care (control group) and regular care + CRR (intervention group).

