#### Secondary endpoints

As secondary endpoints, the same outcome variable will be used to analyse the possible differences between institutions, to separately analyse psychogeriatric and somatic wards, to analyse the medication related events, and to separately analyse each of the parameters included in the combined endpoint (hospital referrals, delirium, falls, and/or deaths).

In order to get this information, physicians will be asked to report any events including: hospital admission, polyclinic visit, emergency department visit, falls, delirium and death. These questions will be asked via an electronic questionnaire via Google Drive. The assessment of whether the event is or could be drug related or not will be done exclusively by the physician.

The quality of life will be measured using the EQ-5D questionnaire both for patients in the control group and patients in the intervention group. The questionnaire will be performed at the end of the study (i.e. after one year follow-up), both for psychogeriatric and somatic patients. The results will be compared between intervention and control group. For both patients groups a caregiver/nurse will answer the questionnaire.

In addition the analysis of the MAI and the cost evaluation will also be performed for both control and intervention group.

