#### Blinding

Blinded for patients; In addition, physicians will be emphatically requested not to talk about the emails.

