### Sample size calculation

Calculation of the total number (one event per patient). The aim is to reduce the number of patients with at least one event with 25% by using the CRR compared to the regular care. These events consist of medication related hospital referrals, delirium, falls, and/or deaths.

In order to calculate the sample size a pilot study was performed. Nursing homes physicians from the region (Envida and Zuyderland) have informed, via an electronic questionnaire, about any hospital referrals, delirium and/or falls within their patients. In addition, they stated whether these events could be medication related. This pilot study has lasted for 5 months. No patient information was given.

The pilot study showed a proportion of patients with at least one event (combination of fall, delirium, hospital referral, and death) in the control group of 0.16 and a mean number of patients per physician of 56.

Assuming a proportion of patients with at least 1 event during 1 year follow-up of 0.20 in the control group, a 25% reduction by using the CRR compared to regular care, i.e. proportion reduces from 0.20 to 0.15, and a two-sided significance level (α) of 0.05, the number of patients per group required to detect an effect with 80% power equals 906. Accounting for the design effect (randomisation per physician; DE = 1 + (m-1)*ICC), where we assume an intra-class correlation coefficient (ICC) of 0.01, a mean number of patients per physician (m) of 56 (pilot study), and a 10% dropout rate, the required number of patients increases to 1562 per group.

We assumed a higher proportion of patients with at least one event in the control group (0.20) than the one found in the pilot study (0.16), because the number of falls were underreported in the pilot study and the follow-up duration is now longer, i.e. one year instead of five months.

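### The article says physicians are blinded, but the intervention physicians receive and answer the alerts, and the same physicians report every primary event

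*Protocol article*

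**What the plan says.** All references are to the protocol article.

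- **Study design** declares: "This study will be blinded for physicians and for patients".
- **Blinding** is narrower: "Blinded for patients; In addition, physicians will be emphatically requested not to talk about the emails".
- **Overall study design** makes the physician the unit of allocation: "The randomisation will be per main nursing home physician and stratified per ward".
- **Intervention group**: "The messages delivered by the CRR will be sent via mail to the specific physicians", one mail per remark. A reply is then required: "In response to the report, the physician will send a feedback message within 36 h", stating whether the advice was followed, not followed or changed.
- **Control group**: the CRR also screens these patients, but through a filter. The alerts are unblinded only at the end of the study. Physicians in both arms receive the same weekly event questionnaire.
- **Primary endpoint**: "All these events will be reported by the nursing home physician via the electronic questionnaire". The events are hospital referral (specialist referral, emergency visit or admission), delirium, fall and death.
- **Secondary endpoints**, on drug-relatedness: "The assessment of whether the event is or could be drug related or not will be done exclusively by the physician".

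**The concern.** The two statements on blinding disagree, and the conduct of the trial settles which one can be true. A physician who receives remarks and must answer them within 36 hours knows that he or she is in the intervention arm. A physician who receives none can infer the control arm. Asking physicians not to talk about the mails limits contamination between them. It does not blind the person who records the outcome.

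This matters because that person supplies the primary endpoint. The components are exposed to different degrees:

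- **Falls and delirium** depend on the physician noticing the event and reporting it. They are the main route for bias.
- **Specialist referral** is the physician's own decision, so knowledge of the arm may change behaviour as well as reporting.
- **Death, hospital admission and emergency visit** are documented facts and are less exposed.

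Reporting could shift either way. A physician who has just acted on advice may expect fewer events and report fewer. One made more alert by the remarks may report more. The drug-relatedness judgement is also exposed, because in one arm it is made by someone who has read the software's remarks on that patient's drugs.

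**Working it through.** **1. The contradiction.** This step needs no arithmetic. Study design claims blinding of physicians and patients. Blinding claims it for patients and refers to mails that physicians know about. Intervention group has physicians receive and answer those mails. The absence rule under Randomisation adds a further case: a control physician who stands in for more than six weeks gets the mails for the intervention patients only, and so can tell the two groups of patients apart. The first statement is incompatible with the others.

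**2. The plan's own sample size.** Inputs from Sample size calculation: 0.20 versus 0.15, two-sided α 0.05, power 80%, intra-class correlation 0.01, 56 patients per physician, 10% dropout.

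- Two-proportion formula, pooled variance, no continuity correction: 906 per group, as stated.
- Design effect = 1 + (56 − 1) × 0.01 = 1.55.
- 906 × 1.55 / 0.90 = 1560.3, rounded up to 1561, against the stated 1562. The figure reproduces and is not in dispute.
- Effective patients per group = 1562 × 0.90 / 1.55 = 907. At 0.20 versus 0.15 this gives power 0.80, as planned.

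**3. Illustration with no true effect.** The reporting rates are assumed; the documents give none. The true proportion is 0.20 in both arms, and a fixed share of event patients goes wholly unreported.

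95% versus 85% reported:
- Reported proportions: 0.20 × 0.95 = 0.19 and 0.20 × 0.85 = 0.17.
- Ratio = 0.17 / 0.19 = 0.895, a 10.5% apparent reduction. As a share of the 25% target: 10.5 / 25 = 42%.
- Standard error = √[2 × 0.18 × 0.82 / 907] = 0.0180, so the critical difference is 1.96 × 0.0180 = 0.0354.
- Two-sided rejection probability = 0.197 + 0.001 = 0.198.

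95% versus 90% reported:
- Reported proportions: 0.19 and 0.18.
- Two-sided rejection probability = 0.079 + 0.006 = 0.085.

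**4. Sensitivity to the number of events per patient.** The endpoint is at least one event in a year, so a patient is lost only if every event is missed. With k events per event patient, each reported independently with probability r, the reported proportion is 0.20 × [1 − (1 − r)^k]. For r = 0.95 versus 0.85:

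| Events per event patient (k) | Reported proportions | Ratio | Two-sided rejection |
|---|---|---|---|
| 1 | 0.1900 vs 0.1700 | 0.89 | 0.198 |
| 2 | 0.1995 vs 0.1955 | 0.98 | 0.055 |
| 3 | 0.2000 vs 0.1993 | 1.00 | 0.050 |

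The inflation is almost gone at two events.

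**5. The other direction.** If the planned effect is real (0.15) but intervention physicians over-report by 10% in relative terms (again assumed), the reported proportion is 0.165 and power falls from 0.80 to about 0.49. At 5% over-reporting the proportion is 0.1575 and power is about 0.66.

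**The case against.** The strongest reply accepts that the sentence is wrong and disputes how much follows from it. Most of that reply stands.

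- **The size is assumed.** The 20% figure needs omission of whole patients, or single-event patients, and the same reporting gap for every component including death. It belongs at the upper end of a range, as step 4 shows.
- **The pilot.** A reader might infer that reporting is already known to be biased, because the Sample size calculation concedes that "the number of falls were underreported in the pilot study". The document does not support this. No intervention arm is described in the pilot, so the remark shows incomplete reporting, not a difference between arms. Equal under-reporting creates no false effect when there is none.
- **Symmetric prompting.** Both arms get the same weekly questionnaire, which should narrow any gap. It does not remove the reporter's knowledge of the arm.
- **Partial safeguards exist.** Each component is already analysed separately, and the medication-related analysis is already secondary. Relabelling the latter as supportive would add little. What the article does not set out is a single composite of the less exposed components.
- **Verification.** A reader might treat the lack of a record check as a fault in itself. This is a condensed article, and source verification may be described in the full protocol or analysis plan, so no such fault is claimed.

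It is also fair to say that physicians can hardly be blinded to an intervention delivered to them. Being open-label is not the error. Claiming blinding is.

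**Conclusion.** The concern holds. The article states a design property that the trial does not have, and the sentence must be corrected. Because the unblinded physicians report every primary event, the composite carries a risk of differential reporting in either direction, concentrated in falls and delirium.

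The size of that risk is unknown. Under the assumptions shown, two-sided rejection with no true effect ranges from about 5%, when event patients have two or more independently reported events, through about 8.5% for a 5-point gap in whole-patient reporting, to about 20% for a 10-point gap. A reader might infer that the false-positive rate is in fact 20%, or that any reporting gap passes in full into the effect estimate. The documents support neither inference. They contain no reporting rates, the at-least-one-event definition dilutes the gap, and some components are hard to misreport.

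**What to change.** 1. Correct Study design to say that patients are blinded and physicians are not, and bring it into line with the Blinding section.
2. Pre-specify a sensitivity analysis of the composite restricted to death, hospital admission and emergency visit, using the primary logistic mixed model with the same fixed factors and physician as random factor.
3. State that the primary result, and the medication-related result that rests on the physician's attribution, will be interpreted in light of unblinded reporting.

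The cost is a weaker blinding claim, a few changed sentences and one extra model run. The restricted composite will have fewer events and less precision, so it should be read for consistency of direction and size rather than for significance.

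Optionally, admissions and emergency visits can be checked in both arms against the patient records that the Hospital costs section says will be used, where these are already held. That section does not establish that the records contain falls without referral, deaths in the home or delirium. Extending the check to those events across 3500–4500 residents would be a substantial task and is not asked for here.
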